#### Intervention

The intervention implements a cross-sectoral all-encompassing multimodal delirium prevention and management approach, and will be carried out in each study center after the center is randomized to take part in the intervention phase of the trial:All personnel training: within 4–6 weeks before the start of the intervention phase, nurses and therapeutic, medical, and support staff involved in the care of study patients will be trained with respect to dementia and delirium care, delirium diagnosis, and depression using a standardized training plan. Staff will be trained to three different levels of expertise: more than 70% of the staff are to receive basic training (90-min training time); more than 20% of nurses are to receive advanced training (“delirium scout” training—450-min training time); and more than 10% are to receive expert-level training (“delirium champion” training—900-min training time). Additionally, at least 70% of the physicians will receive 90 min extra of specific training about delirium risk, diagnosis, treatment, and prevention. The courses will be adjusted to the specific surgical and anesthesiological departments and special care units in order to ensure comparable levels of knowledge between different study sites.Environmental orientation support: the hospital environment will be adapted to the special needs of the patients. The decline of sensory function in older adults often leads to additional psychosocial stress, and is exacerbated by cognitive impairment. To address these issues, appropriate posters and signage will be placed on the wards, and in patients’ rooms and restrooms. Tools for temporal and situational orientation will be made available; for example, whiteboards with personal information, date, season, and year, as well as analog clocks that can be seen from the bed. Moreover, appropriate tools to prevent falls will be provided, such as anti-sliding socks. Special boxes for glasses, hearing aids, and dentures, as well as sleeping masks and ear plugs will be within reach of the patients at all times.Preadmission phase: the trained staff will implement some nonpharmacological preventive interventions in this phase, including informative talks and written recommendations for patients, and instructive contacts with the referring doctors regarding the age-appropriateness of prescribed medications and interventions.“Best practice” multimodal intervention: participants at the respective centers will receive perioperative and postoperative multimodal delirium prevention and care management between 8 a.m. and 8 p.m. on 7 days of the week, modified according to best practice models such as the Hospital Elder Life Program (HELP) [26], “The old patient in the surgery room” [22], or the Care of Confused Hospitalised Older Persons (CHOPs) [27]. Psychogeriatric nurses and one physician who have received 900 additional minutes of “delirium champion” training will form a multiprofessional consultation–liaison-like intervention team that will contact the patients and address their special needs daily. They will facilitate the implementation of the treatments advised in international delirium prevention guidelines [17, 23]: adaptation of surgery and anesthesia, medication and pain treatment appropriate for the patients’ age, pain monitoring, avoidance of movement restrictions such as catheters or infusions, and avoidance of benzodiazepines and anticholinergic drugs. These specialists will prescribe meaningful individualized daily activities for preventing delirium, defined in six modules: reorientation, cognitive activation, mobilization, meal companionship, clinical diagnostics and operation room attendance, and nonpharmacological sleep promotion and anxiety reduction. A team of nurses’ aides or volunteers (mostly gap-year social work volunteers) will carry out these activities, as well as chaperone patients during the diagnostic procedures, and in the operating and recovery rooms. They will receive 40 h of theoretical and practical training on the modules, and will be available daily in two shifts of 12 h per day.Patients and their family members will be advised individually about delirium risk and prevention, and will receive information materials (leaflets, posters, etc.) about delirium and the care service. Moreover, family members will provide individual information about the patient, facilitating individualized care and communication, and will be advised to support some individualized delirium prevention activities.

Given the patient-centered care research implementation goal of this study, the outcomes of patients undergoing the intervention will be compared to the outcomes of patients receiving treatment as usual (TAU) provided by the centers before the randomized start of the intervention.

Patient group involvement and staff involvement has been implemented in an earlier version of this intervention approach adapting the HELP (Hospital Elderly Life Program) structure (see [18]). In addition, we will implement focus groups at the general practitioner level post hospital stay to further evaluate patients’ perception of the intervention itself.

#### Adherence to intervention

The training modules are expected to play a fundamental role in improving adherence to the intervention protocols. They will be supplemented by additional talks, case discussions, and a web-based knowledge base providing webinars, training videos, and so forth. Moreover, a support system for the intervention teams will be established comprising an email service and a telephone hotline, as well as a data pool on a project server. Modules prescribed by the intervention team will be monitored, and the time span of the intervention will be daily documented. Furthermore, adherence to the manuals and “prescription checklists” will be tested by unannounced visits to every site.

#### Adverse events

Adverse events and serious adverse events (SAEs) will be recorded and documented. Falls, strokes, infections, and other severe perioperative complications (death, reoperation, pneumonia, sepsis) are to be expected in this patient group independently of the intervention, while SAEs related to the intervention are expected to be very rare. An example of a study-related SAE could be, for instance, a patient’s fall during early mobilization by the delirium companion during the active intervention phase. The feasibility of the project and the occurrence of SAEs will be assessed every 3 months by the REDMB, who will also carry out audits every year. In the case of substantial differences between the SAEs in the different groups, this will be discussed by the REDBM.

#### Withdrawal

The criteria for discontinuing the intervention for a participant will be death; or study withdrawal requested by the patient, guardian, or authorized relative; or (re)operation of more than 1 h (cut-to-suture time) during the first perioperative week, given that in this case a delirium or POCD cannot be precisely assigned to the first operation; or malignancy surgery with prognosis under 15 months, neoadjuvant chemotherapy, brain radiotherapy, or primary metastasis surgery for pancreas or bronchial cancer.

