#### Outcome assessment

The assessment of all the outcomes will always be performed by trained assessors, who will be blinded for the intervention. Specifically, delirium raters will be told that the data will be used for validating a delirium risk score. Staff will be instructed not to reveal the nature of the intervention to these assessors.

The *primary outcome* will be delirium prevalence. It will be measured by daily delirium screening (I-Confusion Assessment Method-based scoring system for delirium severity (I-CAM)/CAM-S)) [28, 29] over 7 days after surgery and after 2 and 6 months, the Nursing Delirium Screening Scale (NuDESC) [30] (days 2 and 6 after surgery), a chart review at discharge applying the DSM-V delirium criteria as a reference standard [31], and the clinical evaluation.

The CAM [32], with its four-step diagnostic algorithm, is a widely used screening test for assessing delirium. Originally developed from the DSM-III-R, it is now predominantly used for delirium screening and research according to the DSM-IV and DSM-V criteria. It has been operationalized and translated into German [33], and then revealed a high sensitivity of 0.77 in a cohort of geriatric patients with a high prevalence dementia, and a specificity of 0.96–1.00 with excellent inter-rater reliability (Cohen’s κ = 0.95 (CI 0.74–1.0) for the algorithm, single item’s κ values varied between 0.5 and 1).

The I-CAM (I for ICD-10) [28] extends the German version of the original CAM adding abnormal psychomotor activity, to allow taking also the ICD-10 delirium diagnosis as a reference standard and assessing the motor delirium subtypes as well. The CAM-S [29] is a CAM-based scoring system for assessing delirium severity and was operationalized for use with the German version of the I-CAM. As the CAM might be confounded by the fluctuating nature of delirium, we use a chart-based review [31] filled out by trained medical staff at discharge to evaluate for fluctuations in sleep–wake rhythm or psychomotor activity indicating delirium.

The NuDESC is a five-item scale based on nurses’ observations assessing disorientation, inappropriate behavior and communication, hallucinations, and psychomotor retardation over a 24-h period. For the German version of the NuDESC, in a sample of patients after elective surgery, a sensitivity of 0.98, a specificity of 0.92, and an inter-rater reliability of 0.83 were observed [34].

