#### Statistical analysis

For the primary outcome, logistic regression analyses with cluster adjustment are planned.

For the secondary outcomes, the changes in the medication and the care burden of the patients’ relatives, we plan analyses using mixed linear and logistic regression models, with fixed and random factors for estimating heterogeneity over clusters [68].

Subgroup analyses for specific patient groups (e.g., patients with cardiac surgery regarding cognitive status or patients with brief hospital stays/brief surgeries) are planned.

For planned validity assessments of postoperative delirium, the validity of the I-CAM-S and NuDESC vs the RASS will be evaluated as screening tools for postoperative delirium. Diagnostic test performance of the tools will be evaluated by receiver operating characteristics (ROC) analysis.

Missing data (due to nonadherence of a department or a particular patient) will be documented. We will apply mixed-effect models, which handle the missing data without using any imputation method. Mixed-effect models assume that the missing data are missing at random (MAR); that is, when the probability that an outcome is missing is related to some other fully observable variable in the model, but not to the variable with the missing value itself [69].

Regarding the health-economic evaluation, a micro-costing analysis will be carried out using data from the clinical administration of two hospitals (Tübingen and Stuttgart). Moreover, for the patients insured by a specific health insurance (AOK Baden-Württemberg) who consent, the health and care insurance costs of the 12 months before and after surgery will be calculated using a difference-in-difference approach [70]. In this case, the target parameter is the cost per avoided POCD. The cost-effectiveness of the intervention will be calculated comparing the costs of the intervention group and the control group. In addition, quality-adjusted life years (QALYs) will then be calculated using data from the EQ-5D-5 L form about health-related quality of life, and applied for calculating the incremental cost-effectiveness. When possible, subgroup analyses will be carried out, for example, by age or gender, to determine whether cost-effectiveness is different in the corresponding groups. Sensitivity analyses will also be performed. The evaluation will be carried out following the recommendations of the “Good practice secondary data analysis” (GPS).

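### The rule on reoperation in the first week implies that these patients' outcomes are not counted, which would be a post-enrolment exclusion inside the primary outcome window

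*Protocol article*

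**What the plan says.** All references are to the protocol article.

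- **Withdrawal.** The list opens with "The criteria for discontinuing the intervention for a participant will be death" and continues with study withdrawal, several prognosis and cancer criteria, and a (re)operation of more than 1 h cut to suture "during the first perioperative week, given that in this case a delirium or POCD cannot be precisely assigned to the first operation". No other reason is given for the reoperation item.
- **Outcome assessment.** Delirium is screened daily "over 7 days after surgery and after 2 and 6 months". The daily screening covers the same week as the reoperation trigger.
- **Adverse events.** Falls, strokes, infections and "other severe perioperative complications (death, reoperation, pneumonia, sepsis) are to be expected" in this population, independently of the intervention.
- **Statistical analysis.** "For the primary outcome, logistic regression analyses with cluster adjustment are planned". On missing data: "We will apply mixed-effect models, which handle the missing data without using any imputation method".

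The article does not say whether delirium and POCD assessments continue after such a reoperation, or whether ratings already made are kept.

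**The concern.** The literal subject of the rule is the intervention, but its reason is about the outcome. Safety and feasibility are not mentioned. The stated problem is that a delirium could not be credited to one operation, and that is a reason for not counting the delirium. The heading and the placing beside death and study withdrawal point the same way. Usual-care patients have no study intervention to discontinue, so if the rule applies to them at all it can only mean leaving the study or its outcome assessment.

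Read in this way, the rule selects patients on an event that happens after enrolment and during the primary outcome window. The article itself gives grounds for linking that event to both sides of the comparison:

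- **To delirium.** The Background names anesthesia and surgical procedures as triggers of delirium, and associates delirium with falls, infections and other complications.
- **To the intervention.** The Intervention section includes mobilization and the adaptation of surgery and anesthesia. Adverse events gives a fall during companion-led mobilization as an example of a study-related serious event.

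The trial asks whether one care model produces less delirium than another. That question can be answered without deciding which operation caused a given episode. Dropping these patients would give up the comparison of everyone enrolled, and could discard delirium already rated before the second operation.

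**Working it through.** **Planned contrast.** The Sample size section assumes 25% under usual care and 15% under the intervention: 25 − 15 = 10 points, and 10/25 = 40% relative, which agrees with the aim in the Design section.

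**Assumptions (none is in the documents).** Let r be the share of patients with a reoperation of more than 1 h in the first week, and d the delirium risk among them. With P the true rate in all patients of a phase, the rate after removing them is

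observed rate = (P − r·d) / (1 − r).

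**1. Equal shares and equal risk (r = 3–8% in both phases, d = 40%).**
- r = 3%: usual care (0.25 − 0.012)/0.97 = 24.5%; intervention (0.15 − 0.012)/0.97 = 14.2%; contrast 0.10/0.97 = 10.3 points.
- r = 8%: usual care (0.25 − 0.032)/0.92 = 23.7%; intervention (0.15 − 0.032)/0.92 = 12.8%; contrast 0.10/0.92 = 10.9 points.
- With no true effect both phases change alike, so the difference stays zero.

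**2. Equal shares, with the intervention also working in reoperated patients (d = 40% and 24%, the same 40% relative reduction).** The contrast is (0.10 − 0.16·r)/(1 − r).
- r = 3%: 0.0952/0.97 = 9.8 points.
- r = 8%: 0.0872/0.92 = 9.5 points.

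**3. Unequal shares (2% in one phase and 8% in the other, d = 40–60% in both).**
- 2% usual care, 8% intervention, d = 60%: 0.238/0.98 − 0.102/0.92 = 24.3% − 11.1% = 13.2 points. With d = 40%: 11.9 points.
- 8% usual care, 2% intervention, d = 60%: 0.202/0.92 − 0.138/0.98 = 22.0% − 14.1% = 7.9 points. With d = 40%: 9.2 points.
- No true effect (25% in both phases), d = 60%: 24.3% − 22.0% = 2.3 points, with the sign depending on which phase has more reoperations. With d = 40%: 1.0 point.

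**Does the missing-data approach repair this?** No. If delirium is one yes/no outcome per patient, a patient with no counted outcome adds nothing to the logistic model. Removal triggered by a post-enrolment event tied to delirium also strains the missing-at-random assumption on which the article relies.

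**The case against.** The strongest counter-argument is textual. The rule speaks of discontinuing the intervention. Nothing says that ratings stop or that data leave the analysis, and the definition of the analysis set may properly be left to an analysis plan that is not shown. That stands in part: exclusion is inferred, and the absence of a defined analysis set is no finding. What remains is a rule the article does state, with a reason that makes sense only for the outcome.

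The size can also be challenged. Only operations of more than 1 h count, which lowers the affected share. Adverse events expects reoperation independently of the intervention and has the monitoring board discuss substantial differences in serious events between groups. If shares and risks are equal, the null is preserved and the contrast hardly moves. The larger figures need a fourfold imbalance, which nothing in the article suggests. All of this stands.

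Restricting the question to the index elective operation is arguably a legitimate choice of target. But the event that defines the restriction occurs after enrolment, so that analysis suits a supporting role better than the primary one.

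Two stronger readings are tempting and are not supported:

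- **Removal only in the intervention phase.** A reader might infer this because only those patients have an intervention to discontinue. With r = 3–8% and d = 40%, the 15% would fall to 14.2–12.8%, a spurious gain of 0.8–2.2 points. This joins two readings that do not fit together. If the rule only stops the modules, it is one-sided but loses no data. If it removes outcomes because they cannot be attributed, the reason applies equally under usual care.
- **The prognosis and cancer criteria as events known only after surgery.** The article does not say so. Neoadjuvant chemotherapy precedes surgery, and expected survival under 15 months is already an exclusion at entry.

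**Conclusion.** The concern holds as a risk of bias created by a stated rule. It does not establish that patients will be excluded, or that the result is distorted in a known direction. The heading and the attribution reason imply that outcomes after a first-week reoperation of more than 1 h are not counted, in either phase.

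The size rests wholly on assumed shares and risks. With equal removal the effect is small: the contrast moves by less than one point in either direction, and the null is preserved when risks are also equal. With the assumed imbalance of 2% against 8%, the shift runs from about −2.1 to +3.2 points around the planned 10, and up to 2.3 points could appear where there is no effect. The likely distortion is modest, but a change of wording avoids it.

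**What to change.** - Separate discontinuing the intervention from withdrawal from outcome assessment.
- State that every enrolled patient, including those reoperated, continues the scheduled delirium and POCD assessments unless consent is withdrawn or the patient dies.
- State that each patient is analysed in the primary comparison by the cluster's phase at the index operation.
- Report the number of reoperations of more than 1 h by phase, so that readers can judge any imbalance.
- Use exclusion, or censoring at reoperation, only as a sensitivity analysis with the same rule in both phases.

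The cost is a few sentences and some ratings at visits that are already scheduled (daily screening, discharge, and 2, 6 and 12 months). The downside is a somewhat more mixed set of causes of delirium in the primary outcome. Whether the intervention modules should continue clinically after a reoperation is not addressed here.

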#### Outcome assessment

The assessment of all the outcomes will always be performed by trained assessors, who will be blinded for the intervention. Specifically, delirium raters will be told that the data will be used for validating a delirium risk score. Staff will be instructed not to reveal the nature of the intervention to these assessors.

The *primary outcome* will be delirium prevalence. It will be measured by daily delirium screening (I-Confusion Assessment Method-based scoring system for delirium severity (I-CAM)/CAM-S)) [28, 29] over 7 days after surgery and after 2 and 6 months, the Nursing Delirium Screening Scale (NuDESC) [30] (days 2 and 6 after surgery), a chart review at discharge applying the DSM-V delirium criteria as a reference standard [31], and the clinical evaluation.

The CAM [32], with its four-step diagnostic algorithm, is a widely used screening test for assessing delirium. Originally developed from the DSM-III-R, it is now predominantly used for delirium screening and research according to the DSM-IV and DSM-V criteria. It has been operationalized and translated into German [33], and then revealed a high sensitivity of 0.77 in a cohort of geriatric patients with a high prevalence dementia, and a specificity of 0.96–1.00 with excellent inter-rater reliability (Cohen’s κ = 0.95 (CI 0.74–1.0) for the algorithm, single item’s κ values varied between 0.5 and 1).

The I-CAM (I for ICD-10) [28] extends the German version of the original CAM adding abnormal psychomotor activity, to allow taking also the ICD-10 delirium diagnosis as a reference standard and assessing the motor delirium subtypes as well. The CAM-S [29] is a CAM-based scoring system for assessing delirium severity and was operationalized for use with the German version of the I-CAM. As the CAM might be confounded by the fluctuating nature of delirium, we use a chart-based review [31] filled out by trained medical staff at discharge to evaluate for fluctuations in sleep–wake rhythm or psychomotor activity indicating delirium.

The NuDESC is a five-item scale based on nurses’ observations assessing disorientation, inappropriate behavior and communication, hallucinations, and psychomotor retardation over a 24-h period. For the German version of the NuDESC, in a sample of patients after elective surgery, a sensitivity of 0.98, a specificity of 0.92, and an inter-rater reliability of 0.83 were observed [34].

The *secondary outcomes* will be: delirium duration as described in the primary outcome assessment; prevalence of POCD 2 and 6 months after surgery; and persistence of POCD after 12 months. The prevalence of POCD will be measured by the following neuropsychological test battery: the Montreal Cognitive Assessment (MoCA) [35], the digit span backwards [36], the Trail Making Test A and B (TMT A and B) [37], and cognitive performance measured with the continuous nonstandardized test values of these scales. A cognitive deficit is defined as the presence of a test value of ≤ 0.5 standard deviations, normalized for age, gender, and education, in one of these test procedures.

The MoCA is a brief cognitive screening test for assessing cognitive impairment among older people. The test assesses multiple cognitive domains including visuospatial ability, executive functions, memory, attention, language, abstraction, and orientation. The MoCA has high sensitivity (0.90) and specificity (0.87) to detect individuals with mild cognitive impairment and distinguish them from cognitively intact older people [35] and is available in three parallel versions.

The digit span backwards is commonly used to assess working memory capacity. Participants are required to recall a sequence of spoken digits in reverse order. For people older than 70 years, the digit span backwards had a test–retest reliability > 0.60 and an internal consistency of 0.882 [38].

The TMT is a widely used instrument in neuropsychological assessment that measures the speed of scanning and visuomotor tracking, divided attention, and cognitive flexibility [36]. The test consists of two parts, A and B. TMT A requires an individual to draw lines sequentially connecting consecutive numbers from 1 to 25. TMT B involves drawing a similar line, connecting an ascending sequence of numbers and letters in an alternating manner. In a sample of healthy older adults, Part A had a test–retest reliability of 0.78 and Part B of 0.73, and Part A an inter-rater reliability of 0.99 and Part B of 0.93 [39]. In a sample of elderly volunteers, Part B had a sensitivity of 0.63 for cognitive dysfunction, 0.72 for dementia, and 0.77 for AD, and a specificity of 0.89 [40].

For *baseline assessment*, the following variables will be evaluated. Basic sociodemographic patient information to be collected includes age, gender, weight, height, dominant hand, marital status, immigrant background, educational level, occupation, living arrangements, nicotine consumption, alcohol consumption, falls, and statutory level of care dependency. The self-reported subjective memory impairment (SMI) will be assessed, for which subjects will be asked “Do you feel that your memory is getting worse?” (no; yes; I don’t know). If the patient answers yes, the patient will then be asked whether he or she is worried about this (no; yes, that worries me; yes, that worries me very much; I don’t know, no answer) [41]. The personal medical history, including comorbidities, is to be quantified by the expanded version of the Charlson’s comorbidity Index (CCI) [42]. The patient’s preoperative physical status will be assessed by the American Society of Anesthesiologists Physical Status classification (ASA) [43]. The risk of stroke will be estimated with the CHA_2_DS_2_-VASc score (Congestive heart failure/left ventricular dysfunction, Hypertension, Age > 75, Diabetes, Stroke/transient ischemic attack/thromboembolism, Vascular disease, Age 65–74, Sex category) [44]. Laboratory results (hemoglobin, sodium, creatinine, total amount of protein, C-reactive protein), the history of delirium in the past, and a neurological examination will be recorded. The grip strength as a frailty marker will be measured with the Jamar® Hydraulic Hand Dynamometer. Hearing and visual integrity will be tested by the whisper and visual acuity tests [45]. Functional mobility and risk of falls will be investigated by the Timed Up and Go Test (TUG) [46]. Anxiety and depression will be assessed by the Patient Health Questionnaire (PHQ-4) [47]. The health-related quality of life will be measured by the EuroQol five dimensions questionnaire (EQ-5D-5 L) [48, 49] (this version includes five levels of severity in each of the existing five EQ-5D dimensions) and by the 12-Item Short Form Survey (SF-12) [50, 51]. Nutritional status will be assessed by the Mini Nutritional Assessment Short Form (MNA-SF) [52, 53]. Functional status will be evaluated with the Hamburg Classification Manual [54] version of the Barthel Index [55]. Frailty will be analyzed with the Clinical Frailty Scale of the Canadian Study of Health and Aging (CSHA Clinical Frailty Scale) [56]. Pain will be measured by the Numerical Rating Scale of Pain (NRS Pain) [57]. Sleeping behavior will be investigated by the Pittsburgh Sleep Quality Index—Basic (PSQI-Basic), a four-item version of the PSQI [58]. Sleep apnea will be screened for by the STOP-BANG questionnaire (Stop-BANG) [59]. Olfactory function will be scrutinized by the Sniffin’ Sticks 12 version [60]. Cognitive decline will be assessed by the very short version (seven items) of the Informant Questionnaire on Cognitive Decline in the Elderly (IQCODE) [61]. The subjective burden of the family caregivers will be measured by the German Zarit Burden interview (G-ZBI) [62, 63]. Classification as a geriatric patient, will be assessed with the Geriatric-Check using the geriatric concept of Baden-Württemberg (GC) [45]. Finally, the patient’s medications will be recorded, including the type, dose, and frequency of administration.

For *planned analysis*, the following variables are currently anticipated: anxiety and depression will be evaluated with the PHQ-4 questionnaire, the health-related quality of life with the EQ-5D-5 L questionnaire and the SF-12 survey, the nutrition status with the MNA-SF, the functional status with the Barthel Index, and the frailty with the CSHA Clinical Frailty Scale and hand grip. The duration and extent of use of physical restraints and patient care attendants will also be assessed. Moreover, the relevant aspects of behavior in daily life will be assessed by the Nurses’ Observation Scale for Geriatric Patients (NOSGER II) [64, 65], the presence of cognitive decline will be assessed by IQCODE evidenced by relatives, and the subjective burden of family caregivers by G-ZBI. The timelines are summarized in Fig. 3.

